### Outcome Measures

All outcome measures (see Tables 3, 4, 5, 6 and 7) will be administered by blinded assessors at baseline, 6 months and at 18 months follow-up. Each test is chosen because of excellent psychometric properties and minimal sensitivity to practice effects. Cognitive testing takes place in a fed state (after breakfast), and before any physical testing on that day to standardize known effects of fasting and acute exercise on cognitive performance.

**Table 3 T3:** Primary and secondary cognitive and functional outcome measures

Outcome measure	Explanation	Description
Primary Cognitive	Alzheimer's Disease Assessment Scale (ADAS-Cog) [25]	This subscale of the ADAS, measures severity of cognitive dysfunction associated with Alzheimer's disease and is widely used in pharmacological studies of dementia and MCI [51]. The ADAS-Cog has excellent psychometric properties being valid and reliable, and is endorsed as a standard outcome measure [26].

Primary Functional	Bayer-Instrumental Activities of daily Living (B-ADL) [26,52]	The B-IADL initially developed for pharmaceutical clinical trials to assess deficits in the activities of daily life in community-dwelling individuals with MCI and response to pharmacological agents [26], is a 25-item informant or proxy questionnaire.

Secondary Cognitive	Mini-Mental State Examination (MMSE)[29]	Internationally known brief measure to screen for cognitive impairment [41], with valid and reliable quantitative assessment of severity of cognitive impairment, and is sensitive to changes in cognitive function over time [53].
	
	GP-Cog [54]	Six item self report scale identifying whether patients have greater difficulty functioning in 6 areas of daily life compared to their level of functioning 5-10 years earlier.
	
	Clinical Dementia Rating (CDR) [28]	A commonly used clinical tool for the global assessment of dementia severity, is completed by a clinician after synthesizing information obtained from the patient, informants and any other sources [28].

	Subjective Memory Complaint (SMC)	Eight questions were developed to measure SMC including type of memory difficulty, concern level, duration, comparison to peers, and reported by informant, meeting criteria for the assessment of SMC [55].

	Life Experience Questionnaire (LEQ)[19]	Questionnaire is a self report questionnaire examining the amount and quality of mental activity a person has engaged in over their life time [19].

	Matrices	Matrices, a perceptual subtest of the Wechsler Adult Intelligence Scale-III (WAIS-III) assesses executive functions and requires visual perception, organization, and synthesis of visual spatial information [56].

	Similarities	This verbal subtest from the WAIS-III is used to measure verbal conception formation and abstraction [56].

	Trail Making Test (TMT)[40] A and B	Trials A and B test speed of attention, sequencing and visual search, and includes a motor response component, whilst B also assesses mental flexibility, an executive function [57].

	Logical Memory	The Logical Memory subtest of the Wechsler Memory Scale 3^rd ^edition (WMS-III) is used to measure both immediate and delayed memory for verbal information.

	Benton Visual Retention Test (BVRT)[42]	This widely used visual memory test assesses visual perception and visual constructive abilities as participants are required to draw from memory simple designs [41].

	Symbol Digit Modalities Test (SDMT)	SDMT, first published in 1973 by Aaron Smith and subsequently revised in 1982[41] measures divided attention, visual scanning, tracking, and motor speed. It uses a substitution format presenting symbols with matching numbers, and participants are required to name the numbers corresponding to each given symbol.

	Category Fluency	Category Verbal Fluency measures verbal production of animal names from semantic memory [58].

	Controlled Oral Word Association Test (COWAT)	COWAT is a language based task assesses association fluency, and is often used as a measure of executive functioning. The most commonly used letters are F. A. S. or C. F. and L. based upon word prevalence rates [58].

	Memory Awareness Rating Scale-Memory Functioning (MARS-MF) [43]	The MARS-MF is an 11 item self report rating scale of everyday memory functioning. Ratings are made on a 0 - 4 scale where 0 = never and 4 = always, and is usually administered in an interview format [43].

**Table 4 T4:** Secondary outcome measures continued: Psycho-social status

Outcome Measure	Name of scale	Description
Psycho-social	Geriatric Depression Scale (GDS) 15-items [49]	The GDS is used to assess an older person's level of depression with simple yes/no response set [59], and the fifteen item screening test has been reported to be satisfactory [49].
	
	Depression Anxiety and Stress Scale 21(DASS) [60]	21-item self-report measure of severity of depression, anxiety, and stress psychological symptoms. Overall Distress can be calculated by summing each of the sub-scale scores with possible scores ranging from 0-63, with higher scores indicating higher distress [48].
	
	
	Scale of Psychological Wellbeing (SPWB) [47]	The SPWB measures well-being and psychological functioning includes six subscales: autonomy; environmental mastery; personal growth; positive relations with others; purpose in life; and self-acceptance [47]. Participants are required to rate agreement on a six point agreement scale, with higher scores indicating greater wellbeing.
	
	Duke Social Support (DSS)[50]	The DSS is used to assess perceived adequacy and size of social support network on a 3 point scale with higher total scores reflecting higher levels of social support [50].

Quality of life	Life satisfaction Scale (LSS)[44]	This single item 7 point delighted-terrible rating scale provides a gestalt measure of life satisfaction, and can yield reliable and valid data [61].
	
	Physical and Mental Health Summary Scales (SF36)^®^	The Physical & Mental Health Summary Scales include eight generic health concepts, selected from 40 included in the Medical Outcomes Study (MOS), and MOS researchers selected and adapted questionnaire items and developed new measures for a 149-item Functioning and Well-Being Profile [62] the source for SF-36^® ^items.
	
	Quality of Life Scales (QoLS)[46]	This 16 item 7 Likert type delighted-terrible self report scale measures satisfaction with five conceptual aspects of life notably material and physical wellbeing; relationships with other people, social, community and civic activities; personal development and fulfilment; and recreation [46].

**Table 5 T5:** Secondary outcome measures continued: physical health and functional status

Outcome Measure	Explanation	Description
Body composition	Anthropometrics	Standing height body weight, waist circumference are obtained in triplicate after 12 hour fasting and body mass index (BMI)) is calculated as fasting body weight (weight kg/height m^2^).
	
	Bioelectrical Impedance Analysis (BIA)	Whole-body skeletal muscle mass (kg) (SMM)* and fat free mass (kg) (FFM) ** were calculated using the average resistance and reactance values of three sequential BIA measures using the BIA Analyser (RLJ Prizum, S/N: B10875E, Mode; BIA-101S).

Cardio-vascular	Pulse Wave Analysis	Pulse Wave Velocity (PWV) Pulse Wave Analysis (PWA) Heart Rate Variability (HRV) is determined using the SphygmoCor Unit and SphygmoCor software.
	
	Ankle Brachial Index (ABI)	Clinton MI) Ankle-brachial index (mean of dorsalis pedis and posterior tibialis/brachial BP in both arms).
	
	Blood Pressure (BP)	Orthostatic hypotension (OH) Orthostatic Blood Pressure Measurement is taken in a fasted state and after rising from a five minute rest in supine position. Twenty-four hour ambulatory BP monitoring, awake and nocturnal means and circadian rhythm are also obtained.

Exercise Capacity	Muscle strength and endurance	Maximal strength measurement will be obtained using the digital K400 Keiser pneumatic resistance machines (Keiser Sports health Equipments, Inc. Fresno, CA). See **table 7 **for details.
	
	6 minute walk distance (6MWD) [63]	Walking endurance was assessed using the six minute walk test which is a proxy for overall cardiovascular endurance capacity (aerobic capacity) and in the elderly subject it may be determined by muscle strength and endurance, balance, orthopaedic or neurologic abnormalities, and other problems[63].
	
	Aerobic Capacity	Maximal exercise capacity assessed on treadmill walking test (stress test).

Physical performance	Gait speed habitual and fast	Habitual and maximal gait velocities is assessed for 2 m (Ultra-timer: Raymar, Oxfordshire, UK) with the average of two times taken as habitual (CV = 8.7%) and maximal (CV = 7.6%) gait velocity respectively.
	
	Gait analysis (Gait Logger)	Participants walk two walks of 2 minute duration and data is recorded using the gait logger Minion EGaitLogger and downloaded
	
	Isometric handgrip strength	Isometric handgrip strength of the non dominant hand is assessed using a JAMAR handgrip dynamometer (Sammons Preston, Bolingbrook, IL)
	
	Chair stand [64]	This test is used as a proxy for lower extremity power, or the ability to generate high forces rapidly, with participants primarily utilising the hip extensor and knee extensor muscle groups [64].
	
	Static Balance	Static balance is assessed up to 15 seconds in five different positions (feet apart in parallel stance, feet together in parallel stance, half tandem stance, tandem stance, and one legged stance), without the use of assistive device with eyes open. Total static balance is calculated by summing the time recorded for each of the six stances[65].
	
	Tandem walk	Subjects complete a 3 meter forward tandem walk along a marked course with and without a cognitive distracter task (verbal fluency)
	
	Stair climb	The purpose of this test is to climb stairs as rapidly as possible to enable the calculation of Power (Watts). Power is calculated from the formula: P (watts) = (M × D) × 9.8/t Where: M = Body mass (kg), D = Vertical distance (m), t = Time (s) and, D = vertical height of the staircase = height of 1 step in meters × number of steps (if they are all the same height).

*Skeletal muscle mass (SMM) = 0.401(height in cm^2^/resistance in ohms)+3.825 (sex: male = 1; female = 0)+age in years(-0.071) + 5.102 [66]

**Fat-free mass (FFM) = -4.03 + 0.734 (height in cm^2^/resistance in ohms) +0.116(body weight in kg) + 0.096 (reactance in ohms) +0.984 (sex: male = 1; female = 0)[67]

**Table 6 T6:** Secondary outcome measures continued: Health status

Outcome measure	Explanation	Description
Health Status	Habitual Physical Activity level	Daily physical activity, sedentary behaviour and sleep quality and quantity are measured with two Actigraph monitors worn for seven days. The actigraph on the waist measures physical activity and the wrist sleep quality, with data analysed using the ActilifeGTIM (version 2.2.3) and ActiWebClient (version 4.2.2) programs.
	
	Cortisol	Five saliva cortisol samples will be collected using the Salivette (Sarstedt Aktiengessllschaft and Company; Kirschbaum & Hellhammer, 1994) and according to manufacturer instructions. A control 'resting' "Pre" and "Post" samples will be taken before exposure to each 'stressor' condition fasting and upon awakening and 30 minute rest, and a prior to stressor and immediately after the termination of the stressor condition. The cognitive 'stressor' condition is Alzheimer's Disease Assessment Scale (ADAS-Cog) assessment during screening and at 6 months assessment (approximately 45 min), the physical stressor is the second exposure to a set of maximal strength testing (1RM testing) at baseline and 6 mo.
	
	Medical History	Physician complete medical history and physical and neurological examination.

Inflammatory/Anabolic/Deoxyribo-Nucleic Acid (DNA) profile	Serum samples for nutritional, biochemical and hormonal factors, pro- and anti-inflammatory cytokines	A venous blood draw is taken after a 12 hour fast for B12, folate, Thyroid Stimulating Hormone (TSH), insulin, glucose (with calculation of insulin sensitivity and beta−cell function using the HOMA2 Computer Model), Liver Function Tests (LFT), cholesterol (Total, High Density Lipoprotein, Low Density Lipoprotein, Triglycerides), Full blood count, creatinine, albumin, homocysteine, and 25−OH vitamin D level, and a second sample taken to measure specialist markers of inflammation: high sensitivity C−reactive protein (hs−CRP), cytokines InterLeukin (IL)−1b, IL−6, IL−8, IL−10, IL−12p70, IL−18 and Tumor Necrosis Factor− proteins (TNF-proteins), as well as Brain Derived Neurotrophic Factor (BDNF), Insulin Growth Factor-1 (IGF-1). At Baseline only a blood draw is taken for genetic Testing for Apolipoprotein allele 4 (APOE 4).

**Table 7 T7:** Secondary outcomes continued: neuroimaging

Outcome	Measure	Description
Structural MRI: T1-weighted Whole Brain Measures	1. Voxel Based Morphometry	A combination of different software packages will be used for automated and semi-automated computational neuroanatomical analyses, in addition to expert manual tracing of hippocampus and entorhinal cortex.
	2. Cortical thickness	
	3. Whole brain volume	
	4. GM volume	
	5. WM volume	
	6. CSF volume	
Regional Measures	1. Automated regional cortical volume measures	
	2. Manually traced subcortical volumes	

FLAIR-weighted MRI	White matter hyperintensity volume	Automated measure of white matter disease load

Magnetic Resonance Spectroscopy (MRS) Relative measures of :	1. N-acetylaspartate (NAA)	Measures of different brain metabolites using MR spectroscopy in the hippocampus and posterior cingulate grey matter.
	2. Cholines	
	3. Myo-inositol	
	4. Creatine+Phosphocreatine	
Resting State functional MRI	1. Bilateral hippocampal connectivity	Seed-based correlational analysis and Independent Component Analysis will be used to characterise individuals' resting state BOLD time series.
	2. Hippocampus functional connectivity map	
	3. Posterior cingulate functional connectivity map	
	4. Default Mode Network (DMN)	
	5. DMN-anticorrelations	

#### Primary outcomes

Cognitive function is measured via the Alzheimer's Disease Assessment Scale-Cognitive (ADAS-Cog) [25], and capacity to perform daily tasks by the Bayer-Activities of Daily Living (B-IADL) [26] which has been found to differentiate between normal ageing and mild to moderate dementia [39].

#### Secondary Outcomes

##### Cognitive function

Global cognitive function is assessed via the Clinical Dementia Rating scale (CDR) [28], and Mini-Mental Status Examination (MMSE) [29]. Specific cognitive functions are assessed by Trail Making Test A and B [40], Matrices and Similarities subtests of the Wechsler Adult Intelligence Scale 3^rd ^Edition (WAIS-III), Symbol Digit Modalities Test (SDMT) [41], Logical Memory I and II subtests of the Wechsler Memory Scale 3^rd ^Edition (WMS-III), Benton Visual Retention Test-Revised 5^th ^Edition (BVRT-R) [42] and verbal fluency (Controlled oral words association test, and animal names). Subjective perception of memory capacity is assessed by the Memory Functioning Scale of the Memory Awareness Rating Scale (MARS-MFS) [43]. Cognitive domain scores will be calculated on the basis of sum of z-scores of index tests, referenced to whole-group baseline results.

##### Psychosocial and quality of life

Psycho-social wellbeing and quality of life are assessed via the Life Satisfaction Scale (LSS) [44], Physical and Mental Health Short-36 (SF-36>)[45], Quality of Life Scales (QOLS) [46], Scale of Psychological Well Being (SPWB) [47], Depression, Anxiety, Stress Scales (DASS) [48], the Geriatric Depression Scale (GDS) [49], and Duke Social Support (DSS) [50].

##### Physical status and level of functional capacity

Physical status and exercise capacity are assessed across seven domains: body composition; cardio vascular profile; exercise capacity; functional performance; nutritional status; health status; and inflammatory and anabolic profile, with measures described in Table 4.

##### Neuroimaging

MRI data are acquired at baseline, 6 months follow up and 18 months follow up, using a 3.0-Tesla Philips Achieva System (see Table 7). For each time point, brain structure is assessed using a T1-weighted whole brain scan (sequence: T1TFE; TR/TE: 6.39/2.9 ms; slice thickness 1.0 mm without gap; field of view: 256 × 256; resolution 1 × 1 mm) and a T2 FLAIR scan (sequence: TIR; resolution: 0.488 × 0.488 × 3.5 mm; TR/TE = 10,000/110 ms). ^1^H-MRS follows in two volumes of interest: left hippocampus (20 mm M/L, 15 mm D/V, 30 mm A/P, oriented along the hippocampus) and posterior cingulate grey matter (20 mm M/L, 20 mm D/V, 20 mm A/P) using the PRESS sequence (TE/TR = 30/2000 ms, 1024 points, 256 averages). Finally, a resting state functional MRI is conducted using T2* echo-planar BOLD sequence (TR/TE = 2000/30 ms, 200 volumes) with the subject's eyes closed.

### Covariates

Covariates specified *a priori *are age, gender, educational history, occupational history, burden of chronic disease (medications and diagnoses), nutritional supplements, history of weight loss in past year and habitual physical activity level.

### Statistical Analysis

We will use an intention to treat (ITT) analytic strategy as our primary analytic treatment of the data. However, we acknowledge the potential bias of any method of imputation [last observation carried forward (LOCF), mean of group, expectation maximization algorithm (EM)] or restriction to observed cases (complete case analysis). Therefore, we will make all attempts to retrieve data from dropouts by obtaining final measures regardless of intervention participation or compliance, and will use the EM method for data missing at random. In addition, we will compare characteristics of dropouts to completers and perform secondary sensitivity analyses (completers, and per-protocol analyses) to examine potential for dropouts and imputation to bias the results.

Mixed modelling of 6- and 18-month outcomes, adjusted for baseline values and any potential confounders identified will be constructed to test our primary and secondary hypotheses. We will test for main effects of CT and PRT, as well as for the interaction term (CT × PRT) to identify isolated and combined training arm significance and effects sizes. Relationships of interest and risk factors for changes in cognitive function and other secondary outcomes will be analysed with simple and multivariate linear and logistic regression models as appropriate. Weighted mean differences, 95% Confidence Intervals and Effect Sizes will be calculated for all outcomes, and clinical meaningfulness will be assessed in light of available data on the expected annual rates of change in this cohort for all known primary and secondary outcome variables.

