#### Sample size estimates

Sample size estimates (alpha 0.05, beta 0.20) are based on planned comparisons for the main effects of PRT and CT, as well as the effect of combined training vs. either intervention in isolation on our primary outcome: global cognitive function as assessed by ADAS-Cog. The assumptions are as follows: our meta-analyses [30] and review of published RCTs in older adults [15] reveal Effect Sizes (ES) for a range of cognitive outcomes of approximately 0.60 for cognitive training, 0.59 for aerobic/resistance training, and 0.53 for resistance training, compared to 0.15 for control groups. However, as we are enrolling a cohort with early cognitive impairment, we anticipate a decline of approximately this magnitude (ES = 0.15) over 12 months in our sample, so that the sham control condition would merely offset that decline (ES = 0.0). Thus, we have conservatively powered the study to show an ES of 0.53 for the main effects of both CT and PRT vs. control (n rounded up to 30/group × 4 = 120 required for 4-cell factorial design).

The only two published studies of *combined mental and physical training *[12,16] showed average ES = 0.94 for combined training compared to mental training alone and ES = 1.27 for combined training compared to exercise training alone. Therefore, we have ample power (99.7%) to find a difference of this magnitude between our combined training (n = 30) and isolated training groups (n = 30). Reported dropout from drug trials in MCI is 28% [31] however our experience in fully supervised training of older adults with frailty/chronic disease dropout averages 10-15% over 12 months. Therefore, we will inflate sample size needs for approximately10% drop out rate to account for anticipated attrition (n = 132), and we will recalculate these sample size needs in interim analysis after the first 50 participants have completed 6 months intervention and revise ES and sample size needs if required.

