### Randomisation, concealment, and allocation

A concealed, computer-generated sequence of randomly permuted blocks (block size = 8), stratified by gender and age, is generated by a statistician not otherwise involved in the study (http://www.randomization.com, created by [name], Tufts University). Randomization occurs at the completion of the entire baseline assessment. Where randomization occurs in person, assignments will be placed in sealed opaque envelopes and delivered to subjects by the recruitment officer with subjects designated to 6 months of cognitive training, progressive resistance training, combined cognitive and progressive resistance training, or stretching and video-quiz control group in a 1:1:1:1 ratio. Flow of subjects through the study to date is presented in Figure 3.

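### EM is adopted to fill in missing outcomes for the primary analysis; done as a single conditional-mean fill-in, it either understates standard errors or shrinks the effect, and the planned mixed model makes it unnecessary

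*Protocol article*

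**What the plan says.** The Statistical Analysis section makes intention to treat the primary strategy. It concedes that "any method of imputation [last observation carried forward (LOCF), mean of group, expectation maximization algorithm (EM") may introduce bias, as may restriction to observed cases. It then commits to pursuing final measures from dropouts "and will use the EM method for data missing at random". To check the result it will compare dropouts with completers and "perform secondary sensitivity analyses (completers, and per-protocol analyses) to examine potential for dropouts and imputation to bias the results".

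The next paragraph plans mixed modelling of the 6- and 18-month outcomes, adjusted for baseline, with both main effects and their interaction. It also promises 95% confidence intervals and effect sizes for all outcomes.

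The section does not say whether residual noise is added to EM values, whether several imputations are drawn, whether standard errors are corrected, or whether training arm enters the EM model.

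**The concern.** The section names EM as imputation and later speaks of imputation biasing the results. The natural reading is therefore that EM fills in scores, not that it is an algorithm for fitting a likelihood.

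Conditional-mean fill-in gives each missing score its predicted value, with no scatter around it and no allowance for having estimated the prediction. A model fitted afterwards counts these values as full observations. If the prediction uses arm, the data seem more informative than they are. If it does not, the filled-in scores carry little or no treatment difference and dilute the effect. Either way the tests or the effect estimates suffer for CT, PRT and their interaction.

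The step also gains nothing. Baseline is complete, because the section on randomisation places allocation after the entire baseline assessment. A likelihood mixed model uses incomplete follow-up directly under missing at random.

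**Working it through.** **1. The plan's own sample size.** Inputs from Sample size estimates: "Sample size estimates (alpha 0.05, beta 0.20"), and the study is "powered the study to show an ES of 0.53 for the main effects of both CT and PRT vs. control". Sidedness is not stated; two-sided is assumed.
- n per factor level = 2(1.96 + 0.84)² / 0.53² = 2 × 7.85 / 0.281 = 55.9, so 56, or 28 per cell. The plan has "n rounded up to 30/group × 4 = 120 required for 4-cell factorial design", which agrees.
- With allocation "in a 1:1:1:1 ratio", each main effect compares 60 with 60, for 82.7% power.
- 120 × 1.10 = 132, the recruitment target.

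**2. How much may be missing at 18 months.** The plan allows about 10%. The same section reports 10-15% over 12 months in the team's experience. At a constant rate (an assumption) to 18 months, this gives 1 − 0.90^1.5 = 14.6% to 1 − 0.85^1.5 = 21.6%. Results reports retention above 90% to date.

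**3. Arm in the EM step: analytic check.** Suppose dropouts have no follow-up score, so values are filled in from baseline and arm alone. The filled values lie on the fitted regression. The estimate and residual sum of squares are then those of the m observed cases, but the model counts N = 132. With five coefficients (intercept, CT, PRT, interaction, baseline):

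SE ratio (claimed/true) = √[ (m − 5)/(N − 5) × m/N ]

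Type I error = P( |t on m − 5 df| > SE ratio × t₀.₉₇₅ on 127 df )

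- 10% missing: m = 118.8; √(113.8/127 × 0.90) = 0.898; type I error 7.8%
- 15% missing: m = 112.2; √(107.2/127 × 0.85) = 0.847; 9.7%
- 20% missing: m = 105.6; √(100.6/127 × 0.80) = 0.796; 11.8%

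**4. Arm in the EM step: simulation.** Null 2×2 factorial, N = 132, three visits, 8,000-12,000 replicates per setting, assumed correlations between visits 0.5-0.8, dropout weakly related to baseline. Half of dropout falls before 6 months; none and all before 6 months were also run at 10% and 15%. EM fill-in is followed by baseline-adjusted ANCOVA.

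| Missing at 18 months | SE ratio, 18 months | Type I error, main effect, 18 months |
|---|---|---|
| 10% | 0.89-0.92 | 7.1-8.2% |
| 15% | 0.85-0.88 | 8.4-9.8% |
| 20% | about 0.82 | about 10.7% |

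Further runs with data missing completely at random and correlations 0.6-0.7 gave SE ratios of 0.79-0.80 and type I error of 11.2-12.1% at 20% missing. Hence the range of about 10-12%.

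At 10% missing:
- 6-month test: 5.0% if all dropout comes after 6 months, up to 7.8% if all comes before
- average of both times: 5.5-8.2%
- 18-month interaction test: 7.0-7.9%

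Observed-case ANCOVA at 18 months stayed at 4.5-5.5% throughout.

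**5. Arm left out of the EM step.** Main-effect type I error was 4.8-5.2% at 10-28% missing, so there was no inflation. The effect shrinks instead. If the filled-in scores carry no arm difference, the expected estimate is 0.53 × (1 − missing fraction): 0.53 × 0.90 = 0.477 and 0.53 × 0.80 = 0.424. Simulation (600 runs per setting, correlations 0.6-0.7) gave about 0.48-0.49 and 0.42-0.46. An observed 6-month score carries part of the effect forward, which would explain values above the simple product.

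**The case against.** The strongest reply is that one short sentence in a journal article is being read for detail it does not contain. A reader might infer that the plan prescribes analysing filled-in scores as if they were observed. It does not say so: residual draws, multiple imputation and corrected standard errors are neither mentioned nor excluded. That stands, and the figures are therefore conditional. It does not dispose of the point, because the article chooses a method, classes it with last observation carried forward and the group mean, and ties it to the primary analysis.

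A reader might also infer a type I error of 8-12% for this trial. The planned dropout does not support that: at 10% the figure is about 7-8% at 18 months and can be nominal at 6 months. Reaching 12% needs about 20% missing. The 28% from drug trials is cited only as a contrast to the team's own experience. The commitment to retrieve data from dropouts may bring missingness below dropout.

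Nor can one say that every primary confidence interval is too narrow, since that requires arm in the EM step. Without it the error is a conservative attenuation, though still a biased effect size.

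Finally, the sensitivity analyses are not useless. A completers analysis is close to an observed-case analysis and could expose intervals made too narrow by imputation. What it and the per-protocol analysis cannot do is test dropout driven by unobserved decline. Wanting such a test is a preference, not the correction of an error.

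**Conclusion.** The point holds in conditional form. The article adopts EM as imputation for the primary analysis without any safeguard for imputation uncertainty, and either version of a single conditional-mean fill-in does harm:
- **Arm included:** the 18-month standard error is about 8-11% too small and type I error about 7-8% at the planned 10% dropout, rising to about 8-10% at 15% missing and 10-12% at 20%.
- **Arm omitted:** nominal type I error, but 0.53 is estimated at about 0.48-0.49 with 10% missing and 0.42-0.46 with 20%.

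These sizes rest on ANCOVA stand-ins, assumed correlations (mostly about 0.6-0.7), two-sided testing and N = 132; the planned mixed model was not simulated. At the planned dropout the harm is moderate, but it is avoidable at almost no cost and should be removed before analysis.

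**What to change.** Delete the sentence adopting EM. State that the primary analysis is the mixed model already planned, fitted by REML to all observed 6- and 18-month scores of all randomised participants, with baseline as covariate and CT, PRT and their interaction as factors.

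If imputation is kept, specify multiple imputation with both training factors and their interaction in the imputation model, combined by Rubin's rules.

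The completers and per-protocol analyses may stay, described as not addressing dropout related to unobserved decline. A delta-adjusted analysis, in which dropouts are assumed worse by stepped amounts, is an optional addition.

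The cost is a change of wording, little programming and slightly wider confidence intervals. No new data are needed.
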